### Randomisation: allocation concealment and sequence generation

All participants will be assigned a unique registration number allocated by a central computer following details submitted on a web-based form. This number will be used to identify each randomised participant who has consented to take part. Participants will be randomised by computer, with stratified minimisation by sex, ethnicity (Māori, Pacific, non-Māori non-Pacific), and level of nicotine dependence (> 5 points, ≤ 5 points on the Fagerström Test for Nicotine Dependence [FTND] questionnaire [24]), to ensure a balance in these key prognostic indicators between the intervention and control groups. The randomisation sequence will be concealed from all research staff and will not be able to be manipulated.

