### Sample size

A sample size of 1,310 (655 in each group) is required for this trial. Internal Quitline service evaluations and previous findings from a cessation trial conducted by the Clinical Trials Research Unit have established that the average four week quit rate in people receiving usual care through Quitline is approximately 50% [31,32]. A non-inferiority margin of difference between the group proportions was set at 5% (i.e. the quit rates in the cytisine treatment group will be no worse than 5% less than the rate in the NRT active control group). A sample size of 1,310 will be sufficient to confer 90% power at the one-sided significance level of 0.025 using a binomial test for equivalence. The true four week quit rate in those who receive cytisine was assumed to be 55%, which is midway between the estimated efficacy of varenicline (60%) [8] and NRT [6]. The required sample size incorporates a 20% inflation factor to allow for a sufficiently large dataset to evaluate the intervention based on both the intention to treat as well as the per protocol population. The sample size is adequately powered to also evaluate the non-inferiority of cytisine on two month quit rates. Recruitment will take approximately 18 months based on previously run Quitline trials [32,33], and will aim for a minimum of 25% of participants to be Māori and 15% to be Pacific peoples. The sample size will allow the consistency of effects for Māori and Pacific peoples compared to non-Māori non-Pacific to be assessed.

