#### Treatment effects

Non-inferiority will be evaluated by testing whether the lower bound of the 95% CI for difference in quit rates excludes a 5% difference. In particular, the proportion of participants that have been continuously abstinent at four weeks for both groups and the associated two-sided 95% CI for the difference will be estimated. Non-inferiority of cytisine over NRT will be accepted if the lower bound of the 95% CI around the estimated difference in the primary endpoint event rates lies above 5%. The primary analyses will be carried out on an intention-to-treat basis where participants lost to follow-up will be presumed to be smoking. However, it is increasingly recognised that non-inferiority studies should also be evaluated against a per protocol population defined on the basis of compliance, protocol violations, and missing data [34,35]. Both sets of results are important and will be considered when assessing the study objective. In the case that non-inferiority is evident, assessment as to whether cytisine is superior to NRT will be carried out using the same approach but comparing to a zero difference and applied to the intention to treat population.

Chi-squared analyses comparing the proportion of participants that have been continuously abstinent by treatment group, and incidence rates, RR, risk differences and 95% CI will be calculated. Subsequent secondary analyses involving adjustment for baseline covariates including stratification factors will be undertaken using logistic regression. The consistency of effects for Māori, Pacific peoples, and non-Māori non-Pacific will be assessed using tests for heterogeneity. The distribution of all continuous endpoints will be assessed for normality and skewed data will be subjected to an appropriate transformation before analysis. The change from baseline in symptoms of nicotine withdrawal, AUDIT-C and number of cigarettes smoked per day will be analysed using repeated measures models and adjustment for baseline value.

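### The primary confidence interval ignores the three minimisation factors, and no adjusted risk difference is named to set against the 5-point margin; the cost is a slightly conservative test and a little lost power

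*Protocol article*

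**What the plan says.** The randomisation section states: "Participants will be randomised by computer, with stratified minimisation by sex, ethnicity (Māori, Pacific, non-Māori non-Pacific), and level of nicotine dependence". FTND is split at 5 points, and the stated purpose is "to ensure a balance in these key prognostic indicators between the intervention and control groups".

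The Treatment effects section rests the non-inferiority decision on "the proportion of participants that have been continuously abstinent at four weeks for both groups and the associated two-sided 95% CI for the difference". No stratum or covariate term is attached to it. The section then lists chi-squared comparisons, for which "incidence rates, RR, risk differences and 95% CI will be calculated". Only after that does adjustment appear: "Subsequent secondary analyses involving adjustment for baseline covariates including stratification factors will be undertaken using logistic regression".

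The margin is on one scale only. Under Sample size: "A non-inferiority margin of difference between the group proportions was set at 5" per cent. No margin is given for an odds ratio or a relative risk.

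The closing paragraph of Treatment effects allows a pre-analysis review to reconsider adjustment, but commits to none.

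**The concern.** Minimisation removes most of the chance imbalance between arms in the factors used. If those factors predict quitting, the true sampling variance of the difference is smaller than the simple two-proportion formula says. That formula still counts the variation between strata as if it could fall unevenly on the arms. An analysis that ignores the factors therefore reports an interval that is too wide, and the precision gained by the allocation scheme is not used in the decision.

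The planned adjusted analysis does not clearly make up for this. The article does not say in what form its result will be reported, and it does not name an adjusted risk difference. Without one, the adjusted result has no stated comparison with the 5-point margin. This matters also for the per-protocol set. That set is selected after randomisation on compliance and retention, so minimisation no longer guarantees balance in it.

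What is at stake is some power, and an adjusted analysis that may not be readable against the primary criterion.

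**Working it through.** **The plan's own figure.** Inputs from Sample size: control rate 50%, cytisine 55%, margin 5 points, one-sided 0.025, power 90%, 20% inflation, 655 per arm.

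- n per arm = (1.960 + 1.282)² × (0.50×0.50 + 0.55×0.45) / (0.05 + 0.05)² = 523.
- 523 / 0.8 = 654 per arm, or 1,308 in total, against the stated 1,310. The figure reproduces from the unadjusted formula, so the design calculation also ignores the factors.

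**Baseline power of the primary analysis.** Under intention to treat, people lost to follow-up count as smokers, so all 655 per arm contribute.

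- SE = √(0.4975/655) = 0.02756.
- Power = Φ(0.10/0.02756 − 1.96) = Φ(1.67) = 95.2%.

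**How much variance the factors might explain.** The article gives no prognostic effects and no sex or FTND split. Assumed: 50% female, 50% with FTND >5, mean quit rate 50%. The ethnic mix (25% Māori, 15% Pacific) is the recruitment target. R² is the variance of the stratum quit probabilities divided by 0.25.

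- Weak (odds ratios FTND 0.7, Māori or Pacific 0.8, sex 1.0): stratum probabilities of about 0.567, 0.511, 0.478 and 0.423, with weights 0.30, 0.20, 0.30 and 0.20. Variance 0.0027, so R² = 0.011.
- Strong (0.4, 0.6, 0.8): R² = 0.066.

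**Effect on the test.** With the factors balanced, the true SE is the unadjusted SE times √(1 − R²), which is 0.994 for weak and 0.966 for strong.

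| | Unadjusted formula | R² 0.011 | R² 0.066 |
|---|---|---|---|
| True one-sided error of unadjusted test, Φ(−1.96/√(1−R²)) | 2.5% (nominal) | 2.4% | 2.1% |
| Power at 55% v 50%, adjusted | 95.2% | 95.4% | 96.4% |
| Power at 50% v 50%, adjusted | 44.0% | 44.4% | 46.5% |
| 95% half-width at equal rates, points | 5.4 | 5.4 | 5.2 |

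**Check by simulation.** 3,000 trials per scenario with N = 1,310 and biased-coin minimisation (probability 0.8, assumed) on the three factors. The unadjusted interval was compared with a covariate-adjusted risk difference with robust variance.

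| Odds ratios: sex / Māori or Pacific / FTND >5 | One-sided error, unadjusted v adjusted | Power 55% v 50% | Power 50% v 50% |
|---|---|---|---|
| 1.2 / 0.8 / 0.7 | 2.3% v 2.3% | 95.5% v 95.6% | 45.5% v 45.6% |
| 1.5 / 0.6 / 0.5 | 2.3% v 2.7% | 95.5% v 96.0% | 43.8% v 45.2% |
| 2 / 0.5 / 0.33 | 1.8% v 2.2% | 95.9% v 97.3% | 44.7% v 49.7% |

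Monte Carlo error is about 0.3 points for the error rate and 0.9 points for power near 45%. The last row is stronger than the 1-7% range: the same variance calculation gives R² of about 0.11. The 5-point gain belongs to that row only.

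**Why scale matters.** The odds ratio equivalent to a 5-point deficit depends on the control rate: 0.71 at 20%, 0.78 at 30%, 0.81 at 40%, 0.82 at 50%. At 50%, for example, (0.45/0.55)/(0.50/0.50) = 0.82. No single odds-ratio threshold stands in for the margin.

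**The case against.** The best defence is that the plan is valid as written. The unadjusted difference matches the sample-size calculation, an adjusted analysis is planned, and the discrepancy runs in the safe direction. All of that stands. A false claim of non-inferiority becomes slightly less likely, not more, and the weak scenarios show almost no effect.

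A reader might also infer that the adjusted result will be an odds ratio and so cannot bear on non-inferiority. The article does not support that. It names logistic regression and stops there. A logistic model can be standardised to a risk difference, and the statistical analysis plan, which is not shown, may say so. The fair statement is that no adjusted risk difference is stated.

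A reader might further infer that adjustment would rescue an interval too wide for its margin, since the half-width at equal rates is 5.4 points. It would not: adjustment leaves it at about 5.2-5.4 points under R² of 1-7%, still above 5. That width reflects the margin, the sample size and the assumed 55%.

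The pre-analysis review could bring adjustment forward. It leaves the question open and does not settle it, so the mismatch between allocation and primary analysis remains.

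**Conclusion.** The point holds as a modest one about efficiency and coherence. The primary interval does not reflect the allocation scheme, and the article names no adjusted estimate on the scale of the margin. If the factors are prognostic, the one-sided error is about 2.1-2.4% by formula and 1.8-2.3% by simulation, against 2.5%. The loss of intention-to-treat power at the design rates is about 0.2-1.2 points for R² of 1-7%. At equal rates it is about 0.4-2.5 points over the same range, and up to about 5 points in the strongest simulated case.

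The text of the article establishes the mismatch; the sizes rest on assumed covariate effects, splits and minimisation probability. The required sample size is unaffected, and nothing here invalidates a non-inferiority claim made from the unadjusted interval.

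**What to change.** Define the primary estimate as the risk difference, cytisine minus NRT, adjusted for sex, ethnicity (three levels) and FTND (>5, ≤5). Two routes keep the scale and the margin: a Mantel-Haenszel-weighted stratified risk difference, or standardisation from the logistic model already planned, with a robust or bootstrap interval. Compare the lower bound of its two-sided 95% CI with -5 points in both the intention-to-treat and per-protocol sets. Report the unadjusted difference as a sensitivity analysis.

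The choice should be recorded before the allocation code is broken, so that a borderline result is not open to doubt. The cost is wording in the analysis plan and a few lines of SAS or R. All three factors are recorded before randomisation, so no extra data are needed.

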#### Cost analyses

If the primary outcome of the trial is positive then cost analyses will be undertaken. Cost outcomes will include cost per quitter and cost per person reducing their daily cigarette consumption. These data will then be compared with New Zealand data from Quitline and other NRT service providers, in addition to information from various international studies. This modelling will take a health sector perspective. However, the tobacco expenditure savings to individual smokers will also be calculated (for those who quit and cut down) to give a more societal perspective on the benefits (especially to low-income smokers). This calculation will use data on the daily amount smoked prior to quitting and the price of the particular products smoked. For those who cut down their consumption by a significant margin (i.e. 25% or more), the cost per person reducing their daily cigarette consumption will be calculated.

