Following on from the recently published placebo-controlled trial by West et al. (2011) [17], an appropriate research question to now answer is how the efficacy of cytisine compares to NRT. Such a question is important from a policy and funding perspective to help decide whether to use cytisine as a first or second line agent for smoking cessation treatment or whether to publicly fund the drug. Based on the systematic review mentioned above, the expected difference in efficacy between cytisine (OR = 1.83, 95% CI 1.21 to 2.99)[14] and NRT (OR = 1.74, 95% CI 1.64 to 1.86) [6] is too narrow to feasibly conduct a head-to-head superiority trial. We therefore propose conducting a non-inferiority trial to demonstrate whether cytisine is at least as effective as NRT at increasing quit rates in dependent smokers motivated to quit.

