#### Secondary outcome

The following secondary outcome measures will be assessed at one week and one month after the Quit date in the treatment group only:

• *Information related to the use of cytisine: *Participants will be asked for their views on the use of cytisine as a cessation aid (i.e. whether they would recommend the treatment to another smoker and whether they liked or disliked using the product).

• *Participants' treatment compliance: *Self-reported pill counts (also asked at two months), concomitant cytisine and NRT use (also asked at two months), early stopping of cytisine and reasons why.

The following secondary outcome measures will be assessed in all participants at one week and one, two and six months after the Quit date:

• *The physical signs and symptoms associated with withdrawal: *Assessed using the MPSS [27] in abstinent smokers, measured at one week, one month and two months only.

• *Self-rated chances of quitting: *Measured at one week, one month and two months only.

• *Seven-day point prevalence: *The proportion of participants that have stopped smoking, defined as self-report of having smoked no cigarettes (not even a puff) in the past seven days. Measured at every time point.

• *Continuous abstinence: *The proportion of participants that have stopped smoking, defined as self-report of smoking not more than five cigarettes from the Quit date. Assessed at every time point.

• *Use of cigarettes: *If the participant is smoking at any time point, the following outcomes will be assessed: number of cigarettes smoked per day; proportion of participants who have significantly reduced their daily smoking level (defined as reducing consumption by at least 25% in terms of numbers of cigarettes per day or weight of loose tobacco per day); smoking satisfaction (measured using the mCEQ).

• *Use of NRT: *All participants will be asked about use of any NRT (including type, dosage, flavour, and frequency of use) at every time point.

• *Use of non-NRT methods of cessation: *Participants will be asked about their use of non-NRT methods of cessation such as buproprion, clonidine, nortriptyline, varenicline, acupuncture etc, measured at two and six months only.

• *Alcohol use and abuse: *Measured using the AUDIT-C. Measured at one and two months only.

• *Adverse events: *Information regarding any adverse events and whether they are considered to be related to treatment will be collected at every time point.

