• *Cost information: *Cost outcomes will be derived from known costs of the various products, and will include cost per quitter and cost per person reducing their daily cigarette consumption. The tobacco expenditure savings to individual smokers will also be calculated using data on the daily amount smoked prior to quitting and the price of the particular products smoked.

• *Concomitant medication: *Collected at every time point.

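### The cost analyses are run only if the primary outcome is positive, although cost is listed as a secondary outcome without that condition

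*Protocol article*

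**What the plan says.** The Cost analyses section sets a gate: "If the primary outcome of the trial is positive then cost analyses will be undertaken". It then names cost per quitter and cost per person reducing daily consumption, adds individual tobacco savings, and describes a comparison with outside sources: "These data will then be compared with New Zealand data from Quitline and other NRT service providers, in addition to information from various international studies".

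The Secondary outcome section carries no gate. Its list opens with "The following secondary outcome measures will be assessed in all participants at one week and one, two and six months after the Quit date", and cost is an item in that list: "Cost outcomes will be derived from known costs of the various products, and will include cost per quitter".

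The Background explains why the comparison with NRT is worth making: "Such a question is important from a policy and funding perspective". It mentions the choice of first or second line use and whether to fund the drug publicly.

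**The concern.** One section lists cost as an outcome for everyone, and another reports it only if the primary result goes one way. Followed as written, a listed secondary outcome can disappear because of the trial's own result.

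The missing cases are not ones where cost has stopped mattering. The article presents low cost as a main attraction of cytisine. A cheaper product that narrowly misses a 5-point margin is still a live funding question, and failing to show non-inferiority does not show that the product is not worth funding.

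There is a second, smaller effect. If cost is reported only when the observed difference is favourable enough, the quit rates that feed it are on average somewhat favourable to cytisine.

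**Working it through.** **Inputs.** From Sample size: "A sample size of 1,310 (655 in each group) is required for this trial"; NRT quit rate 50%; cytisine quit rate 55%; margin 5 points; one-sided 0.025; 90% power; 20% inflation. From Treatment effects: non-inferiority is judged on the lower limit of the two-sided 95% CI, taken here as having to lie above −5 points, in line with Sample size. True cytisine rates other than 55% are assumptions, shown as a range.

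**The plan's own figure.** n per arm = (1.960 + 1.282)² × (0.50×0.50 + 0.55×0.45) / (0.05 + 0.05)² = 10.507 × 0.4975 / 0.01 = 523. Allowing for 20% loss, 523 / 0.8 = 654 per arm, or 1,308 in total against the stated 1,310. It reproduces.

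**How often the cost analysis is dropped.** Read positive as non-inferiority in the intention-to-treat population, 655 per arm. With d the true difference (cytisine minus NRT):

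- SE = √{[p_C(1−p_C) + p_N(1−p_N)] / 655}
- smallest observed difference that counts as positive: c = −0.05 + 1.96 × SE
- a = (c − d) / SE
- P(dropped) = Φ(a)
- mean upward shift of the observed difference when the analysis is run = SE × φ(a) / [1 − Φ(a)]

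For equal arms: SE = √(0.50/655) = 0.0276; c = −0.05 + 0.0542 = 0.0042; a = 0.150; P(dropped) = 0.560; shift = 0.0276 × 0.394 / 0.440 = 0.025.

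| True cytisine v NRT | a | P(dropped) | Shift in the difference (points) |
|---|---|---|---|
| 55% v 50% (design) | −1.67 | 0.048 | +0.3 |
| 52.5% v 50% | −0.76 | 0.225 | +1.1 |
| 50% v 50% | +0.15 | 0.560 | +2.5 |
| 47.5% v 50% | +1.05 | 0.854 | +4.3 |

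A binomial simulation with 400,000 trials per case agrees to within half a percentage point on the probabilities.

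**What the shift does to the planned figure.** The planned figure is average cost per quitter, whose denominator is the number of quitters in an arm, not the difference between arms. With near-equal variances the shift splits about evenly: up by half in the cytisine arm, down by half in the NRT arm.

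- Equal arms: 2.5 / 2 = 1.25 points. Cost per quitter changes by 50/51.25 − 1 = −2.4% for cytisine and 50/48.75 − 1 = +2.6% for NRT, so about 2.5% per arm.
- 52.5% v 50%: 1.1 / 2 = 0.55 points, about 1% per arm.
- Design values: 0.3 / 2 = 0.15 points; 0.15/55 and 0.15/50 are both about 0.3%.

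An incremental ratio, with the difference as denominator, would be affected more: 0.3 points on 5 is about 6% at the design values, and 1.1 on 2.5 is about 44% at 52.5% v 50%.

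**Sensitivity to the reading of positive.** The article does not define the word. On 523 per arm, a rough stand-in for a per-protocol requirement, the analysis is dropped 10.0% of the time at the design values and 63.4% if the arms are equal. If superiority were meant, it is dropped 55.8% of the time at the design values with 655 per arm.

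**The case against.** The case for leaving the plan alone has several parts.

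- *The harm is small where the trial expects to be.* This stands. At 55% v 50% the analysis is dropped about 5% of the time and the selection is negligible. The larger figures need a smaller true effect than the protocol assumes.
- *The gate biases the cost result badly.* A reader might infer this from the 2.5-point shift in the difference. The documents do not support it for the planned figure, which is an average by arm and moves by about 2.5% at equal arms. The stronger reading applies only to an incremental ratio, which the article does not describe.
- *Cost is compared only with outside data.* A reader might infer this from the sentence on Quitline and other providers. It over-reads a condensed article. Cost outcomes sit among those for all participants and refer to the various products, so both arms are covered. The external comparison is described as a further step, and nothing excludes a contrast between the randomised arms. Incremental and uncertainty methods may properly be left to the analysis plan.
- *The funding question would go unanswered.* This is too strong. The Objectives contain no cost hypothesis, and the Background sentence concerns comparative efficacy as an input to funding. Quit rates by arm, RR and risk differences are reported without any condition, and product costs are described as known, so a simple cost per quitter could be worked out by others.
- *The two sections do not truly conflict, since one defines the outcome and the other says when it is analysed.* This is a possible reading. Even so, the outcome list then promises something that the analysis section may withhold, and the text should say so in one place.
- *Deferring economic modelling is an open, prespecified choice of resources.* True, but most of the inputs are collected anyway, so little is saved.

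**Conclusion.** The point holds as a cheap improvement to a secondary analysis. The Cost analyses section makes a listed secondary outcome depend on the primary result, and the Secondary outcome section does not. With 655 per arm, 50% on NRT and positive meaning non-inferiority, the outcome is lost about 5% of the time at the assumed 55%, about 22% at 52.5% and 56% if the drugs are equal. Only the first of these rests on the protocol's own effect assumption.

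Selection of the estimate is a minor matter: about 2.5% per arm in average cost per quitter at equality and about 0.3% at the design values. The documents do not support a claim of serious bias, of a missing between-arm comparison, or of an unanswered funding question. The primary conclusion is not touched.

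**What to change.** Delete the condition from the Cost analyses section and align that section with the Secondary outcome list. State that cost per quitter and cost per person reducing consumption will be reported by randomised arm, with the cytisine v NRT difference and its uncertainty, whatever the primary result. Keep the comparison with Quitline, other providers and international studies as context.

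The cost is a little analyst time. Product costs, quit status, consumption and tobacco prices are already planned inputs, so no extra participants or contacts are needed.

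### The planned cost measures are average ratios, which do not show the between-arm difference in cost and quitters, or its uncertainty, on which the funding choice turns

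*Protocol article*

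**What the plan says.** The protocol article names its cost-effectiveness measures twice. Under Secondary outcome: "Cost outcomes will be derived from known costs of the various products, and will include cost per quitter", together with cost per person reducing consumption. Under Cost analyses: "Cost outcomes will include cost per quitter and cost per person reducing their daily cigarette consumption".

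The same section sets a condition: "If the primary outcome of the trial is positive then cost analyses will be undertaken". It then says what the figures are compared with: "These data will then be compared with New Zealand data from Quitline and other NRT service providers, in addition to information from various international studies". It also plans to calculate smokers' savings on tobacco. It states no difference in cost or in quitters between the randomised arms, and it fixes no time point at which a quitter is counted for costing.

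The purpose is given in the Background, on how cytisine compares with NRT: "Such a question is important from a policy and funding perspective". The decisions named there are first- or second-line use and public funding. The margin, under Sample size, is that "the quit rates in the cytisine treatment group will be no worse than 5% less than the rate in the NRT active control group".

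**The concern.** A funder choosing between two drugs needs to know how much more or less one costs than the other, and how many quitters are gained or lost in exchange. Cost per quitter divides each arm's cost by all of its quitters, including those who would have quit on either drug. Two such ratios can rank the cheaper drug first without pricing any quitters forgone.

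This matters more in a non-inferiority trial, where a pass rules out only a deficit as large as the margin. A lower cost per quitter could be read as settling the funding question while the data remain compatible with some loss of quitters, or while a loss appears at a later follow-up.

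**Working it through.** **Inputs.** Control quit rate 50%, cytisine 55%, margin 5 points, one-sided 0.025, 90% power, 20% inflation and 655 per arm (Sample size). Non-inferiority is judged on the lower limit of the two-sided 95% CI (Treatment effects). That section requires the limit to lie above 5%; I read this as above -5 points, in line with Sample size. I take a positive primary outcome to mean that non-inferiority is shown. The article gives no cost per arm and no expected six-month rates, so those below are assumptions.

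**1. The plan's own figure.** n per arm = (1.96 + 1.2816)² × (0.50×0.50 + 0.55×0.45) / (0.05 + 0.05)² = 523. Then 523/0.8 = 654 per arm, or 1,308 in total. With pooled variance, 524.06/0.8 = 655.07 per arm. The stated 1,310 is reproduced.

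**2. What a pass requires at one month.** With about 50% in each arm and 655 per arm, SE = sqrt(2 × 0.25/655) = 2.76 points and 1.96 × SE = 5.4 points. The lower limit exceeds -5 only if the observed difference is at least about +0.42 points. With 524 per arm (655 less 20%), the requirement is +1.05 points.

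**3. What a bare pass leaves open.** At +0.42 points the 95% CI is 0.42 ± 5.4, or about -5.0 to +5.8 points. A true 2.5-point deficit passes with probability 0.146, and a true 5-point deficit with probability 0.025.

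**4. Break-even of the average ratio.** Cytisine has the lower cost per quitter when its cost relative to NRT is below p(cytisine)/p(NRT).

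- Limiting case, 45% v 50%: 0.45/0.50 = 0.90.
- Deficits of 4, 3, 2 and 1 points from 50%: 0.92, 0.94, 0.96 and 0.98.
- Planned 55% v 50%: 1.10, so cytisine is favoured even at up to 10% higher cost.

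**5. Is the limiting case reached at one month?** At an observed 45% v 50%, SE = sqrt((0.2475 + 0.25)/655) = 2.76 points and the lower limit is -5 - 5.4 = -10.4 points. Non-inferiority fails and the cost analysis is not run.

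**6. Later time points.** Continuous abstinence is also recorded at two and six months, and the one-month condition does not screen those results. Take an assumed deficit of 2 points. The break-even is 0.48/0.50 = 0.96 if the control rate is 50%, 0.18/0.20 = 0.90 if it is 20%, and 0.08/0.10 = 0.80 if it is 10%. At 18% v 20%, with assumed costs per participant:

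- 85 v 100 units: 85/0.18 = 472 v 100/0.20 = 500 per quitter, but 15/0.02 = 750 saved per quitter forgone.
- 50 v 100 units: 278 v 500 per quitter, but 50/0.02 = 2,500 saved per quitter forgone.

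The average ratios prefer cytisine both times; only the incremental figure shows the very different terms of the exchange.

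**7. Cost and outcome are linked.** Under Intervention, cytisine participants also receive Quitcards and are told to redeem them only if still smoking at one month or in need of further support after the course. Their NRT cost therefore depends partly on whether they quit. Uncertainty has to be assessed on paired cost and outcome, which separate summaries cannot supply.

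**The case against.** The strongest reply is that the cost analysis follows only a positive primary result, and at the planned rates that means cytisine observed slightly ahead. One-month ratios would then contain no observed lost quitters, and at the planned 55% v 50% a cheaper cytisine is both cheaper and more effective. This stands. A reader might infer that the plan will favour any drug more than 10% cheaper while 5 quitters per 100 are lost. The documents do not support that: the margin bounds the confidence limit, not the observed difference, and an observed 45% v 50% would stop the cost analysis. An observed one-month deficit can pass only if the control rate is about 30% or lower, and then only a small one: at 655 per arm, at most 0.04 points at 30% and 0.70 at 20%.

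It can also be said that the list of cost outcomes is open-ended, that quit proportions and risk differences by arm are planned anyway, and that an article may leave incremental methods to a fuller document. So it would be too strong to say that the trial cannot produce the incremental comparison. But the article does more than stay silent: in both places it names only average ratios, and it names outside data as the comparison. That choice does not fit the question in its Background.

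**Conclusion.** The point holds in limited form. The named cost-effectiveness measures are average ratios, and they give neither the between-arm differences in cost and quitters nor their joint uncertainty. At a bare pass, the data would still be compatible with anything from almost 5 fewer to 5.8 more quitters per 100. A deficit at two or six months could also enter the cost figures, because no time point is fixed.

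The 0.90 break-even at 45% v 50% illustrates the limit only and is not an expected result. The one-month figures assume a 50% control rate, 655 per arm and non-inferiority as the condition. If a positive outcome meant superiority, the one-month interval would exclude a deficit and only the later time points and the missing between-arm differences would remain. All cost values above are illustrative. The primary analysis is not affected.

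**What to change.** Make the main cost result a comparison of the randomised arms at a stated time point:

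- mean cost per participant in each arm, covering all products used, including NRT used by cytisine participants;
- the proportion quit in each arm;
- the difference in each, with a joint bootstrap interval that resamples participants within arm and keeps each person's cost and outcome together;
- the incremental cost per additional quitter, or the saving per quitter forgone, where it can be interpreted.

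Keep cost per quitter, cost per reducer and the comparison with outside data as description.

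No new data collection is needed: NRT use is recorded for all participants at every time point, cytisine pill counts are taken, and product costs are described as known. The price is a little more analysis, plus a stated rule for the product use of participants lost to follow-up. The incremental ratio is unstable when the quit-rate difference is near zero, which is likely here, so the two differences must always stand beside it.
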